## 2. OBJECTIVES

The objectives are to examine in a randomized controlled trial whether:

- 1) feedback on relevant daily life person-context interactions (as measured with MET-D) during pharmacotherapy directly affects treatment response in terms of immediate and follow-up decrease of depressive symptomatology and relapse
- 2) feedback on relevant daily life person-context interactions (as measured with MET-D) during pharmacotherapy is cost-effective
- 3) measurement of relevant dynamic daily life behaviours significantly contributes to the prediction of the future course of depressive symptomatology.
- 4) individual differences in (i) the effect of feedback on daily life person-context interaction and (ii) the predictive value of these person-context interactions can be traced back to genetic differences

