Levels of reward experience, stress sensitivity and affect variability are calculated from the MET-D observations for each subject at the end of each intervention week. Since these are complex phenotypes derived from combinations of data they are not subject to easy conscious manipulation by patients.

Before entering the study, subjects will be screened for a current depressive episode by means of the Structured Clinical Interview for DSM-IV Axis I Disorders (SCID-I) and the Hamilton Depression Rating Scale (HDRS). After inclusion, a saliva sample will be taken for genetic analysis and the subject has to complete the following measurements: Inventory of Depressive Symptoms (IDS) [31], the NEO personality inventory (NEO-PI-R) [32, 33], Childhood Trauma Questionnaire (CTQ) [34], Interview for Recent Life Events (IRLE) [35], Empowerment Questionnaire [36], TiC-P (Trimbos/iMTA questionnaire for Costs associated with Psychiatric Illness) [37], PRODISQ (PROductivity and DISease Questionnaire) [38], and EQ-5D (Euroqol-5D) [39]. Because we hypothesize that the effect of the MET-D feedback on reward experience results in an increase in of empowerment of the subjects, the Empowerment Questionnaire will be used as an additional measurement of the effect of the MET-D intervention. The latter three questionnaires (TiC-P, PRODISQ and EQ-5D) will be used in the costs-efficacy analysis of the MET-D.

All subjects receive additional MET-D training on a separate moment. All groups receive the following pre and post intervention measurements: i) SCID-I interview for diagnosis of depression, ii) HDRS, and iii) IDS. In addition, there are four follow-up measurements of SCID, HDRS and IDS for all groups at 4, 8, 12 and 24 weeks after the end of the intervention, and two follow up measurements of TiC-P, PRODISQ, and EQ-5D for all groups at 12 and 24 weeks after the intervention (see table 1).

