### GWAS approach

Previous experience has learned that the use of candidate gene approaches (i.e. having a specific hypothesis for a specific piece of genetic variation) is a good strategy for disorders with a known pathophysiology, but is insufficient to identify genetic variation for complex disease phenotypes. With a few exceptions, such as Huntington's disease or Parkinson's disease, most phenotypes relevant for the field of neuropsychiatry are considered complex, heterogeneous and of multifactorial causality. Furthermore, their genetic origin is most likely the result of a combination of a large number (>200) genetic variants, each with small effect sizes (Odds ratios around 1.1).

With the advent of new technology that allows to determine sequence variation in about one million genetic markers simultaneously (of the in total approximately 3 million genetic markers that vary between persons), genome-wide association studies (GWAS) have become a new, hypothesis-free research strategy that is especially suited to determine the genetics of complex phenotypes. The use of GWAS in other fields of medicine has resulted in the identification of multiple genetic markers associated with complex phenotypes. For example, more than ten polymorphisms have now been associated with diabetes mellitus type 2, most of which were unknown from candidate gene approaches. GWAS in addition allows for the identification of copy number variants (CNVs), for example deletions, insertions, duplications and complex multi-site variants, that have been shown to be involved in the aetiology of psychiatric disorder.

The drawback of GWAS approaches is that they require huge samples, usually in the order of 20.000 to 60.000 or more subjects, given the degree of multiple testing that needs to be corrected for and the anticipated small effect sizes. Therefore, multi-site international collaboration is the only means to acquire these sample size requirements and MHeNS ascribes to the scientific policy of worldwide sharing of data in order to elucidate the causes of complex disorders. This policy is also mandatory for recipients of funding from the EU, Wellcome Trust, NIH, NIMH, etc. GWAS data collection in

MHeNS is therefore shared anonymously with the various international scientific consortia that study the genetics of schizophrenia, bipolar disorder and other phenotypes and workers of MHeNS are usually involved in the analyses of these data.

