#### Hypothesis-based approach

Since the GWAS research strategy is able to identify small genetic effects on complex phenotypes, but is not able to demonstrate how newly identified *specific* genetic markers contribute to the disease phenotype, a complementary approach is also needed. This complementary approach is hypothesis-driven involving specific genetic variation, aiming to unravel the genetic contribution of novel identified variants to the disease phenotype. Since insights concerning relevant polymorphisms and haplotypes change rapidly, an up-to-date relational (i.e. cross-relating genotype, phenotypic expressions, biochemical pathways) database relevant for the neurosciences is maintained within MHeNS. The mainly replicatory genetic analyses thus are always matched against the most recent information available worldwide. The scientific approach of GWAS identification followed by hypothesis-based replication also represents a tightly organised international effort: one group identifies a novel variant, followed by immediate efforts to replicate by international groups.

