#### DNA analysis

Therefore, each person's complete set of DNA, or genome, is purified from the blood or cells, placed on tiny chips and scanned on automated laboratory machines. The machines quickly survey each participant's genome for strategically selected markers of genetic variation (around 1 million), which are called single nucleotide polymorphisms, or SNPs. Since information relating to 1 million SNPs is difficult to relate conclusively with any complex phenotype by a single research group, anonymized data will be shared within the framework of international consortia. Secondly, since insights concerning relevant markers change rapidly, the DNA of these individuals is stored for 15 years for determination of previously undetermined genetic markers when there is new information that these markers may be relevant to the phenotype studied.

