## 7.3 Study procedures

Subjects are screened for the inclusion criteria, by means of the SCID-I and answer a questionnaire concerning demographic variables. After inclusion subjects:

- undergo a psychiatric interview: HDRS
- fill out additional questionnaires concerning personality (NEO-PI), depression symptomatology (IDS), trauma (Childhood Trauma Questionnaire and Recent Life Event Scale), empowerment (Empowerment Questionnaire), illness and costs due to loss productivity (PRODISQ), illness and illness related costs (TiC-P), and quality of life (Euroqol-5D).
- spit some saliva in special tubes as to measure polymorphisms/haplotypes in the DNA that have been associated in previous studies with the brain reward system and depression.

At base-line:

All subjects will participate in a 5-day MET-D measurement period. After this period, they undergo 2 psychiatric interviews (the depression part of the SCID-I and the HDRS) and

have to complete one self-report questionnaire concerning depressive symptoms (IDS). Subjects are briefed and de-briefed after the ESM period. The ESM debriefing includes the collection of the MET-D devices and discussion concerning unclarities or missing values. See also 'study design' for a more elaborate description.

The intervention period:

Subjects randomized to the 'MET-D intervention *with* feedback' group will participate in a 6-week-period of 3 days a week of ESM (collected by the MET-D) and receive weekly feedback on these measurements. Subjects randomized to the 'MET-D intervention *without* feedback' group will also participate in a 6-week-period of 3 days a week of ESM (collected by the MET-D), but no feedback on the daily recordings is given. In order to prevent any effects of different duration of researcher contacts in both groups, the difference in time is filled by doing two more weekly interviews on anxiety and depression in the 'MET-D intervention *without* feedback' group.

All subjects receive TAU as well during the intervention period.

After the intervention period:

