**9.2 Univariate analysis**

ESM data (as measured with MET-D) have a hierarchical structure. This means that, multiple observations (beep level) are clustered within subjects (subject level). Multilevel regression analysis is suitable for this type of data because it takes the variability associated with each level of nesting into account [40]. The XT MIXED command in STATA 10.1 (Stata Corporation, College Station, Tex, USA) will be used to perform multilevel linear regression analyses. Analyses will be conducted conform previous work [3, 41-46] using multilevel random regression analyses. Technical details have been described in previous studies [3, 41-46]. As described in previous work [3, 41-46], the following positive affect/negative affect phenotypes of daily life emotional response patterns will be constructed from data collected with the Experience Sampling Method:

- i) positive affect (PA)
- ii) negative affect (NA)
- iii) instability of NA indexed by NA variability in daily life
- iv) instability of PA indexed by PA variability in daily life
- v) NA response to negatively appraised daily life events (stress-sensitivity)
- vi) PA response to positively appraised daily life events (reward experience)

First, to analyse the effect of feedback on immediate and follow-up depression scores and relapse we will compare relevant pre, post and follow-up variables between the three groups using multilevel regression analyses.

In addition, multilevel regression analyses are used to examine whether measurements of dynamic daily life person-context interactions (the above mentioned PA/NA affect phenotypes as measured with MET-D) significantly contribute to the prediction of future courses of depressive symptomatology.

Third, to examine whether individual differences in both the effect of feedback on daily life person-context interaction and the predictive value of these person-context interactions can be traced back to genetic differences, we will analyse the effect of genetic polymorphisms on pre, post and follow-up HDRS, SCID-I by means of multilevel regression analysis.

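### Objective 4 leaves the set of genetic variants open and carries no exploratory label, and at the one effect size the protocol cites about 120 people can give only weak evidence on any variant

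*Protocol*

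**What the plan says.** Section 2 lists four objectives. The fourth asks whether individual differences in the effect of feedback, and in "the predictive value of these person-context interactions can be traced back to genetic differences". Section 7.1.2 places it among the secondary parameters. Neither section calls it exploratory.

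The analysis is one sentence in section 9.2: "we will analyse the effect of genetic polymorphisms on pre, post and follow-up HDRS, SCID-I by means of multilevel regression analysis". Under Study Design, "there are four follow-up measurements of SCID, HDRS and IDS for all groups at 4, 8, 12 and 24 weeks" after the intervention, so with pre and post there are at least six occasions for each of the two outcomes.

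On which variants are meant, the protocol says three things:
- Section 7.3 limits the saliva analysis to "polymorphisms/haplotypes in the DNA that have been associated in previous studies with the brain reward system and depression", but lists none.
- Section 7.1.2, Hypothesis-based approach: "The mainly replicatory genetic analyses thus are always matched against the most recent information available worldwide".
- Section 7.1.2, DNA analysis: "the DNA of these individuals is stored for 15 years for determination of previously undetermined genetic markers", when new information suggests that they matter.

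On effect size and sample, section 7.1.2 (GWAS approach) describes more than 200 variants, "each with small effect sizes (Odds ratios around 1.1". It says that multiple testing has to be corrected for, and that genome-wide studies are at a disadvantage because "they require huge samples, usually in the order of 20.000 to 60.000 or more subjects". Section 4.4 plans for 120 participants with complete data and states power for HDRS and for relapse prediction, but none for the genetic objective. Section 7.4 lets patients decline the saliva sample.

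**The concern.** A protocol may leave a candidate list and a multiplicity method to the statistical analysis plan. This one goes further and states that the list will keep moving. Variants can therefore enter the analysis after this trial's HDRS and SCID-I results are known. A plan that froze the list would conflict with section 7.1.2 unless that section were amended.

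The protocol also explains clearly why single variants are hard to detect: small effects, many tests, very large samples. It uses that reasoning to justify sharing data with consortia, and does not carry it over to the within-trial analysis in section 9.2.

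What is at stake is the genetic conclusion only. With an unlabelled objective and an open list, the trial could report that response to feedback, or prediction of relapse, is attributable to a variant that was picked late and rests on a nominal p-value with little weight.

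**Working it through.** **Is there a planned figure to reproduce?** Not for this objective. The powers of 0.93 and 0.95 in section 4.4 concern a 3-point HDRS difference and an odds ratio of 0.5 on relapse. What can be checked is whether the two genetic figures in section 7.1.2 agree with each other. With OR 1.1 per allele, alpha 0.05/1,000,000, 80% power and equal cases and controls (the last two assumed), N = (5.451 + 0.842)² / (0.25 × 2·MAF·(1−MAF) × (ln 1.1)²). This gives 34,875 at minor-allele frequency (MAF) 0.5 and 54,493 at MAF 0.2, both within the protocol's range. So OR 1.1 and the sample range belong together.

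**Inputs for the within-trial test**
- N = 120 (section 4.4).
- OR 1.1 per allele (section 7.1.2), used as a scenario; ln 1.1 = 0.0953.
- Two-sided 0.05, assumed, because section 9.2 names no level.
- Event rate p from 0.2 to 0.5 and MAF from 0.1 to 0.5, both assumed.
- Correlation of HDRS between occasions from 0.3 to 0.7, assumed.

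Power = Φ(λ − 1.96) + Φ(−λ − 1.96), with λ as below.

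**1. Binary outcome, one occasion.** λ = ln(1.1) × √(120 × p(1−p) × 2·MAF·(1−MAF)).
- p = 0.2, MAF = 0.1: λ = 0.0953 × √3.456 = 0.177; power 5.4%.
- p = 0.5, MAF = 0.5: λ = 0.0953 × √15 = 0.369; power 6.6%.
- With N = 100 instead of 120, the range is 5.3% to 6.3%.

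**2. HDRS, one occasion.** The odds ratio is converted to a standardised difference per allele, d = 0.0953 × √3/π = 0.0525, and λ = d × √(120 × 2·MAF·(1−MAF)).
- MAF 0.1: λ = 0.244; power 5.7%.
- MAF 0.5: λ = 0.407; power 6.9%.

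**3. HDRS averaged over six occasions.** λ is multiplied by √(6/(1 + 5ρ)).
- ρ = 0.7 (factor 1.155), MAF 0.1: power 5.9%.
- ρ = 0.3 (factor 1.549), MAF 0.5: λ = 0.631; power 9.7%.

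**4. Variant-by-feedback interaction.** The first part of objective 4 concerns the effect of feedback, so this is the closer test. For the feedback arm against the other two (40 v 80), the variance term is multiplied by (1/3)(2/3) = 2/9. With p = 0.5 and MAF 0.5, λ = 0.0953 × √(15 × 2/9) = 0.174 and power is 5.35%; with MAF 0.3 it is 5.3%. For HDRS at one occasion it is 5.4% at both allele frequencies.

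**Reading the result.** A true null variant reaches p < 0.05 in 5% of tests. The ratio of that chance under OR 1.1 to that under no effect is 5.4/5 = 1.1 to 6.9/5 = 1.4 for a single occasion, and at most 9.7/5 = 1.9 with six occasions averaged. This does not depend on how many tests are run.

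**Sensitivity to the scenario.** At OR 2, power for a variant's main effect on a binary outcome runs from 25% (p = 0.2, MAF 0.1) to 77% (p = 0.5, MAF 0.5). For the interaction at OR 2, λ runs from 0.693 × √(3.456 × 2/9) = 0.607 to 0.693 × √(15 × 2/9) = 1.265, so power is 9% to 24%.

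**The case against.** The strongest reply is that much of this is scenario. The protocol quotes OR 1.1 for variants behind complex neuropsychiatric phenotypes. It gives no size for moderation of feedback or of relapse prediction, and a candidate with a large main effect could be detected. That stands: OR 1.1 is not the protocol's assumption for this test, and at OR 2 the weak-evidence conclusion fails for main effects in the most favourable case. It does not rescue the interaction, where OR 2 still gives at most 24%.

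Further limiting text deserves credit. The objective is secondary, candidates must have been linked before to reward or depression, and the analyses are described as mainly replicatory. These points lower the severity. They do not close the list, since new links can be published after this trial's outcomes are in. Section 11.1 says that collected material is destroyed after analysis, but section 7.1.2 is explicit that DNA is kept.

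Three stronger readings are tempting and not supported:
- **That variants will be tested uncorrected at 0.05.** Section 9.2 names no level. The 0.05 in section 4.4 belongs to the HDRS and relapse calculations, and a correction may stand in an analysis plan that is not shown. Any family-wise error rate would also need a marker count that the protocol does not give.
- **That the trial will search a million markers on its own.** Section 7.1.2 says a single group could hardly relate them conclusively to a phenotype, and sends those data to consortia.
- **That each time point is tested separately.** Section 9.2 specifies multilevel regression, which can pool occasions.

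**Conclusion.** The concern holds in limited form. The protocol states that its marker set stays open, names no variant, gives no error control or power for this analysis, and does not mark objective 4 as exploratory. If variant effects are of the size it cites, power is about 5 to 7% for a single-occasion test, at most about 10% with HDRS averaged over six occasions, and about 5% for a variant-by-feedback interaction, against 5% under no effect. A nominally significant variant would then say little.

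These figures rest on OR 1.1 as a scenario and on the assumed event rates, allele frequencies, correlations and two-sided 0.05. The openness of the marker set rests on the protocol's text alone. Severity is low: the objective is secondary, and a reader should not infer any effect on the comparison of the three arms.

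**What to change.** Amend sections 2, 7.1.2 and 9.2 as follows:
- Label objective 4 exploratory, and state that no claim of genetic moderation will rest on this trial alone.
- Freeze a dated list of candidate polymorphisms before genotype is linked to outcome.
- Apply Holm or false-discovery-rate control across that list and the two outcomes, HDRS and SCID-I.
- Report variants added later from stored DNA as post hoc, and bring section 11.1 on destruction of material into line with the 15-year storage.

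Error control limits false claims but does not create power. For an illustrative five variants and two outcomes, a Bonferroni threshold of 0.05/10 = 0.005 (the first step of Holm) lowers the best-case single-occasion power for a binary outcome at OR 1.1 from 6.6% to 0.8%. The exploratory label is therefore the main part of the change.

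The cost is protocol wording and one dated list, with no new data, samples or visits. The downside is that the genetic results lose confirmatory status.

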**Objective:**

- (1) Does feedback on continuous monitoring with MET-D during pharmacotherapy result in a better treatment response (immediate and follow-up reductions of depressive symptoms, decreased relapse risk)?
- (2) Is feedback on continuous monitoring with MET-D during pharmacotherapy cost-effective?
- (3) Do measurements of daily life person-context interactions improve the prediction of future courses of depressive symptoms?
- (4) Can individual differences in (1) the effect of feedback on daily life person-context interaction and (2) the predictive value of these person-context interactions be traced back to genetic differences?

**Study design:** Randomized clinical trial with three groups of 40 subjects each (2 experimental groups and 1 control group). The first group receives a 5-day pre- and post MET-D assessment *and* a continuous MET-D assessment (3 days of MET-D measurements during a 6-weeks period) *with weekly feedback* (to both patient and therapist) during treatment as usual (TAU). The second group also receives a 5-day pre- and post MET-D assessment *and* a continuous MET-D assessment (3 days of MET-D measurements during a 6-weeks period) but *without feedback* during treatment as usual (TAU). The third group receives a 5-day pre- and post MET-D assessment but no additional intervention during TAU. This is the control group.

**Study population:** A sample of patients (n=120) with a depressive disorder will be recruited within (i) SEARCH, the research network of mental health institutions within Limburg and South-Brabant, The Netherlands, (ii) general practices and (iii) the general population.

**Intervention (if applicable):** The MET-D is a recently developed wearable interactive palmtop suitable for the Experienced Sampling Method (ESM) to study subjects in their daily life. The intervention group receives feedback on MET-D measurements of reward experience in daily life.

**Main study parameters/endpoints:** The rate of change in reward experience measured with the MET-D, and the change in depression symptomatology measured with the Structured Clinical Interview for DSM-IV Axis I Disorders (SCID-I) and the Hamilton Depression Rating

Scale (HDRS). Reward experience is conceptualised as the degree of positive affect following small positive daily events.

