A second aim of this study is to evaluate whether the use of the MET-D, from the viewpoint of the society, is preferable compared to Usual Care in terms of effects (depressive symptoms, relapse), utilities (quality of life), and costs. Based on this main research question several sub-questions are relevant, such as: 1a) What are the (extra) costs of the delivery of MET-D (with and without feedback) compared to Usual Care? 1b) What are the (extra) effects (measured in depressive symptoms, relapse, and quality of life) of MET-D (with and without feedback) compared to Usual Care? We expect that (ii) MET-D feedback on reward experience and affect variation will be cost-effective.

Furthermore, we hope to confirm recent results regarding the role of reward experience, as described above, in the prediction of a depressive relapse [5]. We expect that (iii) the ability to generate reward experience predicts a decreased risk for the development of a depressive relapse. MET-D measurement of reward experience may thus lead to an improvement of the prediction of future courses of depressive symptoms.

Not only person-context interactions, as measured with the MET-D, are important in the etiology of depression and in the prediction of future depressive episodes. Evidence on the important role of genetic influences on both depression as well as on stress sensitivity is emerging [3, 21-27]. For example, subjects who are 'Met' carriers of the BDNF gene exhibit increased stress sensitivity compared to the 'Val/Val' carriers [28]. Since stress sensitivity influences treatment response [4], it can be hypothesized that treatment effect may be partly under genetic control, as is demonstrated by recent findings [29]. This may be due to the intermediate action of stress sensitivity. Therefore, our final goal is (iiii) to examine the influence of genetic differences on both the effect of MET-D feedback on treatment response, and on the predictive value of daily life person-context interactions on relapse risk.

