- (2). Individuals may habituate quickly (i.e. feel bored) if feedback is received on the same issue over and over again. Now, there are new elements and training possibilities added each two weeks, ensuring "novelty".
- (3). A danger of repeating the feedback on the same items for too long is that the participants get too much insight in the construction of the feedback and will, in the end, fill in socially desired information in their daily life recordings to get positive responses from the researcher. Therefore, feedback is construed differently each two weeks. Since participants will not be informed on future items of feedback they cannot provide socially desired responses. (Another characteristic of the design preventing socially desired responses is that the various feedback results are retrieved through statistical associations between several items which cannot be manipulated readily by participants). Therefore, the study will not formally assess socially desired responding tendencies.

The one constant element of feedback over all six sessions, however, is feedback on the association between patients' average positive emotions as assessed with MET-D and their amount of depressive complaints as assessed with SCL-90 depression scale items (filled in each evening in the MET-D device).

In both treatment arms 1 and 2, participants have weekly sessions with the researcher. In treatment arm 2, however, no feedback on the daily recordings is given. In order to prevent any effects of different duration of researcher contacts in both arms, the difference in time is filled by doing two more interviews on anxiety and depression in treatment arm 2 each week. The structure of the sessions is built up according to a standardized protocol. Clear instructions are formulated on how to give feedback and perform the session in a similar manner for each participant. Training is provided to researchers.

In both arms 1 and 2 there is also a debriefing concerning the MET-D measurements at each session. Discussed are things as: why the participant missed some measurements, whether there are any technical problems, whether some things are unclear etc. Furthermore, the participant is encouraged to fill in the MET-D questions next time as accurately as possible conform the instructions of the researcher.

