For the economic evaluation, the Incremental cost-effectiveness ratio (ICER) will be determined on the basis of incremental costs and effects of MET-D (with and without feedback) compared Usual Care. The cost-effectiveness ratio will be stated in terms of costs per outcome rate, the cost-utility ratio will focus on the net cost per QALY gained. The ICER will be calculated as follows.  $ICER = (C_i - C_c) / (E_i - E_c)$ , where  $C_i$  is the annual total cost of the MET-D (with and without feedback) group,  $C_c$  is the annual total cost of the Usual Care group,  $E_i$  is the effects at one year follow-up for the MET-D (with and without feedback) group and  $E_c$  is the effect at one year follow-up for the Usual Care group. The robustness of the ICER will be checked by non-parametric bootstrapping (1000 times) [47]. Bootstrap simulations will also be conducted in order to quantify the uncertainty around the ICER, yielding information about the joint distribution of cost and effect differences. The bootstrapped cost-effectiveness ratios will be subsequently plotted in a cost-effectiveness plane, in which the vertical line reflects the difference in costs and the horizontal line reflects the difference in effectiveness. The choice of treatment depends on the maximum amount of money that society is prepared to pay for a gain in effectiveness, which is called the ceiling ratio. Therefore, the bootstrapped ICERs will also be depicted in a cost-effectiveness acceptability curve showing the probability that MET-D (with and without feedback) is cost-effective using a range of ceiling ratios. Additionally, to demonstrate the robustness of our base-case findings a multi-way sensitivity analyses will be performed. In the sensitivity analysis uncertain factors of assumptions in the base case analysis will be recalculated in order to assess whether the assumptions have influenced the incremental cost-effectiveness ratio (ICER), for example by varying cost-prices and volumes between minimum and maximum [47].

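### Objective 2 asks whether feedback is cost-effective, but the planned ICER has Usual Care as its only comparator and leaves open whether the two MET-D arms are pooled

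*Protocol*

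**What the plan says.** The question about feedback appears three times. The Protocol Summary asks "Is feedback on continuous monitoring with MET-D during pharmacotherapy cost-effective". Section 2, objective 2, asks whether "feedback on relevant daily life person-context interactions (as measured with MET-D) during pharmacotherapy is cost-effective". Section 1 states the expectation that "MET-D feedback on reward experience and affect variation will be cost-effective".

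Section 1 also sets a second aim, which is whether MET-D is preferable to Usual Care from society's viewpoint. Sub-question 1a under that aim reads "What are the (extra) costs of the delivery of MET-D (with and without feedback) compared to Usual Care", and 1b asks the same for effects.

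The analysis is in section 9.2. The ICER is determined "on the basis of incremental costs and effects of MET-D (with and without feedback) compared Usual Care". In the formula, the active cost term is "the annual total cost of the MET-D (with and without feedback) group", the active effect term is worded the same way, and both comparator terms are those of the Usual Care group. The acceptability curve is drawn for MET-D under the same with-and-without-feedback label.

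Arm 2 is described in section 3. It receives the same monitoring as arm 1 without feedback, and contact time is matched: "the difference in time is filled by doing two more interviews on anxiety and depression in treatment arm 2 each week". Section 7.1.1 compares health care consumption and costs between the three groups at baseline, 12 and 24 weeks.

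**The concern.** The question concerns feedback, but the ratio concerns MET-D against Usual Care. Arm 2 is the arm that separates feedback from monitoring and researcher contact, yet section 9.2 never uses it as a comparator for cost per effect.

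The formula can be read in two ways, because it speaks of one MET-D group with and without feedback. If the two arms are pooled, the feedback arm is averaged with its own control and the contrast disappears. If each arm is set against Usual Care, the ratio for arm 1 describes the whole package of monitoring, contact and feedback.

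Cost-effectiveness is one of four objectives, costs are among the main outcomes in section 7.1.1, and section 10.4 links the trial to possible implementation in general mental health care. A reader could take the package ratio, or a pooled one, as the value of feedback.

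**Working it through.** The Protocol states no cost, QALY, ceiling ratio or economic power, so there is no figure of its own to reproduce. The check has three parts.

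**1. Question against contrast**

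| Place in Protocol | Subject | Comparator |
|---|---|---|
| Summary; section 2, objective 2; section 1, expectation (ii) | Feedback | None named |
| Section 1, second aim, 1a and 1b | MET-D, with and without feedback | Usual Care |
| Section 9.2, ICER and formula | MET-D, with and without feedback | Usual Care |
| Section 9.2, acceptability curve | MET-D, with and without feedback | None named |
| Section 7.1.1 | Health care consumption and costs | Three groups, but not as cost per effect |

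No row gives a cost per effect for arm 1 against arm 2.

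**2. What the planned ratio says about feedback**

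Write C and E for cost and effect, with subscripts 1, 2 and 3 for the arms (3 = Usual Care). The Protocol's formula for arm 1 is

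ICER(1 v 3) = (C1 − C3) / (E1 − E3) = [(C1 − C2) + (C2 − C3)] / [(E1 − E2) + (E2 − E3)].

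This mixes the feedback increment, ICER(1 v 2), with the monitoring increment, ICER(2 v 3), weighted by each step's share of the effect. One value of ICER(1 v 3) is therefore compatible with many values of ICER(1 v 2).

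Assumed inputs relative to Usual Care: arm 1 costs +1,000 euro for +0.025 QALY, and arm 2 costs +600 euro. Only arm 2's QALY gain varies.

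| Arm 2 gain (QALY) | Arm 1 v Usual Care | Arm 2 v Usual Care | Pooled v Usual Care | Arm 1 v arm 2 |
|---|---|---|---|---|
| 0.020 | 1,000/0.025 = 40,000 | 600/0.020 = 30,000 | 800/0.0225 = 35,556 | 400/0.005 = 80,000 |
| 0.005 | 1,000/0.025 = 40,000 | 600/0.005 = 120,000 | 800/0.015 = 53,333 | 400/0.020 = 20,000 |

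The pooled cost is (1,000 + 600)/2 = 800. The pooled effects are (0.025 + 0.020)/2 = 0.0225 and (0.025 + 0.005)/2 = 0.015.

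The weights reproduce the first column. In the first row, 0.2 × 80,000 + 0.8 × 30,000 = 40,000. In the second, 0.8 × 20,000 + 0.2 × 120,000 = 40,000.

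The direction changes where 400/(0.025 − x) = 40,000, that is at x = 0.015 QALY for monitoring alone. Above that gain the ratio against Usual Care flatters feedback, and below it the ratio understates its value.

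An extreme case uses other assumed inputs: arm 2 at +300 euro and arm 1 at +800 euro, each gaining 0.020 QALY. Feedback then adds 500 euro and no effect, so arm 1 is dominated by arm 2. Arm 1 against Usual Care is still 800/0.020 = 40,000, and the pooled ratio is 550/0.020 = 27,500.

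**3. Precision of the added contrast**

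With equal standard deviations, the variance of a difference is proportional to 1/40 + 1/40 = 0.050 for arm 1 against arm 2, and to 1/80 + 1/40 = 0.0375 for pooled arms against Usual Care. The standard error is √(0.050/0.0375) = 1.15 times as large as under pooling. Each separate arm against Usual Care is also 40 against 40.

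**The case against.** The strongest reply is that Usual Care is a deliberate choice. The second aim and sub-questions 1a and 1b in section 1 ask for exactly that comparison, and section 9.2 carries it out. This stands: the comparisons with Usual Care are legitimate and should stay. It does not dispose of objective 2, which is worded as a question about feedback.

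Four stronger readings are tempting, and the Protocol does not support them.

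- A reader might infer that the evaluation cannot answer objective 2 at all. That holds fully only if the arms are pooled, which the text neither states nor excludes. If they are kept separate, the increment for feedback follows by subtraction from the same data.
- A reader might infer that the two MET-D arms are never compared economically. Section 7.1.1 does compare costs between the three groups; what is absent is cost per effect.
- A reader might infer that feedback will look worse against arm 2 than against Usual Care. This depends on the assumed inputs and reverses in the second row of the illustration. The Protocol's own hypothesis, that feedback drives the benefit, points towards that row.
- A reader might infer that arm 2 will be charged for the interviews that fill its contact time. Nothing in the Protocol says how delivery cost is built up, so this is not part of the point.

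It can also be said that dominance ordering and curve layout belong in an analysis plan. That is fair for the layout. The comparator and the composition of the active group, however, are already written into the Protocol's formula.

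**Conclusion.** The concern holds as a mismatch between objective 2 and the contrast fixed in section 9.2, together with an ambiguity about pooling. Under pooling the feedback contrast is lost. With separate arms, sub-questions 1a and 1b are answered, but the added cost per effect of feedback over contact-matched monitoring is not a planned result.

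The size is illustrative only. A ratio of 40,000 euro per QALY for arm 1 against Usual Care can accompany a feedback increment of 80,000 or of 20,000, depending on whether monitoring alone gains 0.020 or 0.005 QALY. All costs and effects are assumed, so neither the direction nor the size for this trial can be predicted. Randomisation, data collection and the three-group clinical analysis are unaffected.

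**What to change.** In section 9.2:

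- State that the two MET-D arms are analysed separately and not pooled, and word the formula terms and the acceptability curve accordingly.
- Keep each MET-D arm against Usual Care for sub-questions 1a and 1b.
- Add the incremental costs, effects and ICER of arm 1 against arm 2, with bootstrap and acceptability curve, and name this as the contrast that isolates feedback for objective 2.
- Present the three strategies in one incremental analysis. If arm 2 is dominated, including by extension as in the second row of the illustration (120,000 against Usual Care, then 20,000 for the step to arm 1), the decision ratio for arm 1 is the one against Usual Care. The arm 1 against arm 2 contrast is still reported.

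No new data are needed, since section 3 already plans the cost and quality-of-life questionnaires for all groups. The cost is a little more analysis and a feedback contrast resting on 40 against 40. That is less precise than a pooled comparison, and its ratio will be unstable if the difference in effect between the two MET-D arms is small.
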